### Recruitment

Recruitment began on October 2, 2023, at 4 sites: the Universities of Windsor and Guelph in Canada and the Universities of Michigan and Nebraska-Lincoln in the United States. In year 2 of the trial, recruitment was ended at the University of Nebraska and paused at the University of Michigan due to the departure of the site principal investigators (PIs) from those institutions. In year 3 of the trial, recruitment is planned at the University of Guelph, the University of Michigan, the University of Maryland, and the University of Central Florida. The 6 total sites represent diverse students, sizes, and contexts (eg, rural vs urban, proportion of students in residence, racial, and geographic diversity). Recruitment will only take place during the academic year when classes are in session. Multiple methods are used to attract participants to the study, including (1) recruitment emails through the registrar, faculties, or departments to all eligible students, (2) research participant pools, (3) social media ads or posts to relevant Facebook groups (eg, groups for students at a particular university), and (4) flyers will be distributed at on-campus events, posted in women’s bathrooms on campus, and sent digitally to student newsletters/newspapers, student organizations, or student-specific listserves at the sites of Universities. Not all recruitment methods will be used at all sites (eg, emails are permitted through the Registrar at certain sites but not others).

### Prescreening Survey

Links or QR codes in advertising materials (emails, flyers, and ads) take potential participants to a website that has the semester’s updated survey link or directly to the prescreening survey in REDCap (Research Electronic Data Capture; Vanderbilt University) to determine eligibility. The screener begins with a brief description of the study, followed by the screening survey.

Participants give their initial consent to provide demographic information in the screener to determine their eligibility for this research. Demographic information provided (eg, sexual identity and race/ethnicity) also allows us to see whether recruitment strategies are working to reach diverse students. If participants (1) do not consent to provide demographic information or (2) are ineligible based on the screening criteria, they are sent to a page thanking them for their interest.

Participants attend the IDEA^3^ program in pairs for support and in order to adequately practice and learn the self-defense tactics in the third unit with a partner. Using the same protocol we used in our pilot trial [20], after completing the screening survey, eligible participants are sent to an additional page where they are asked a series of questions about the partner with whom they would be willing to participate. Partners must meet study eligibility criteria. Students can either participate with a friend or consent to be partnered with another undergraduate woman by the study staff. Potential participants must also indicate which one of the intervention session blocks scheduled for that semester they are available for. Although the control arm intervention condition only meets once (see below), participants must state they are available for the 4 dates allotted for the IDEA^3^ program in case they are assigned to the intervention arm of the trial.

Students who wish to participate with a friend are asked to provide their own contact information and the first and last name of their friend. If they are willing to provide the friend’s email address, they can personalize an email invitation sent directly through REDCap, or if they prefer to communicate with their friend first, we send them an email they can forward to that friend with a link for them to sign up. If that friend is not interested, students have the option of proceeding in the study with a match done by the research team or discontinuing their involvement. If they believe their friend has already signed up for the study, they can indicate this and, if verified, that person is contacted to ensure they are willing to be matched with the student. Participants who do not provide the name for a potential program partner and are unwilling to be partnered with another student by study staff are sent to a page thanking them for their interest, as they are not eligible for the study. Referred program partners progress through a similar prescreening process via an emailed REDCap link. Once both partners have completed the prescreening survey and have screened as eligible for the study, they are “matched” and their ID numbers are linked in REDCap.

Partnered participants are introduced (if they were not already friends) by email and invited to get in touch to discuss where they will get together to participate. Further, they are provided with a link where they can schedule their individual screening interview or request further information.

### Screening Interview and Informed Consent

Interested students who meet the initial prescreening criteria and have been successfully matched with a partner receive an email with a link to book a 30-minute screening interview using Calendly. Up to 5 reminder emails/texts are sent over a 10-day interval until the student schedules an interview or is presumed to be no longer interested in the study. When potential participants book, they are sent a confirmation of their interview time and date, a Zoom link with instructions on how to use Zoom, and the full consent form to review before the interview. The main points from the consent form are reviewed aloud with the participant by the study staff, and questions are answered. Participants provide consent verbally at the start of the scheduled interview (or, if not given, participants are thanked, and the interview is ended). The screening interview is conducted by an intervention facilitator and potential participants are required to turn on their camera for the interview as (1) this allows additional screening for age and gender eligibility and (2) participants are required to come to intervention sessions with cameras on, and using a camera during the screening interview confirms they have a working camera that they can use during intervention sessions.

Facilitators review the format of the intervention with participants to make sure the participant is willing and able to meet in person with the partner and that they have a suitable and safe space to participate together. Facilitators assess any physical limitations that might affect participation in the self-defense portion of the program (to inform adaptations for accessibility if they are assigned to the intervention arm), ensure participants feel comfortable using Zoom, and ensure participants have a stable Wi-Fi connection. They are asked if they are willing to sign up for a GroupMe account and be included in group messages to other participants assigned to their intervention block using this app. GroupMe is a messaging app designed for multi-person chats. Facilitators use this app to send messages to participants in the IDEA^3^ arm (after they come to the first session and learn their assignment), about upcoming program sessions, resources, etc. Participants do not have to have a GroupMe account to receive these messages, but they need one to chat with other participants. For participants who have requested to be partnered with someone they do not know, this interview allows them to discuss any concerns/reservations about this process and go over where they need to meet their partner before their first or only program session. Both partners in each participant pair will be required to individually complete this one-on-one interview and provide informed consent before being allowed to enroll in the study.

### Randomization

When participants have completed their screening interview, they receive an email inviting them to complete the baseline survey (see section below on assessments for more details). The baseline survey must be completed no less than 24 hours before their first program session (or only program session for control participants). The email contains an individualized URL taking them directly to this first survey, which takes 30-45 minutes.

Randomization of the pair will occur once both participants in the pair complete their screening interview and baseline survey, and no later than 24 hours before the first (or only) session. If one member of the pair fails to complete the baseline survey, the other member of the pair will be given the choice of continuing in the study with a different partner (time permitting), rescheduling for a later intervention session, or discontinuing the research. In rare circumstances, that is, if the participant has been re-paired once or more, there is insufficient time to re-pair, or no one else is available for a new pairing, she will be individually randomized and permitted to complete the intervention by herself. Once the pair is randomized, they are sent a Zoom link for the session through REDCap. This link does not identify their random assignment. The facilitators/research assistant (RA) reveal the assignment once everyone is present in the Zoom room at the scheduled time.

The trial biostatistician is responsible for setting up the randomization protocols in REDCap. Randomization is stratified by site using permuted block sizes of 2 and 4, and participant pairs are randomized 1:1 to the IDEA^3^ program or control. Randomization occurs after baseline completion so that participation in the trial cannot be affected by knowledge of intervention assignment. The site coordinators generating the random assignment for a participant pair are not able to view the random allocation sequence.

### Interventions

#### Both Arms

After providing informed consent in the screening interview and before the first (or only) session, a Program Resource Kit is delivered to participants by mail (if time permits) or hand-delivered by study staff. Kits include some sealed envelopes (marked unit 1-4) with resources necessary for both the control and intervention arms, with instructions not to open the envelopes until they are instructed to do so at their first intervention session. Kits also include some snacks and small “swag” items. Both arms receive identical kits. Receiving gifts and snacks before the first session also encourages attendance at the first session.

#### Intervention Condition

The IDEA^3^ SA resistance program follows the same structure as EAAA, with four 3-hour units led by 2 near peer-facilitators with content designed to help women more quickly and effectively recognize and resist coercion (see the *Introduction* section for more detail). IDEA^3^ retains the interactive modality of EAAA by using games, discussions, and other activities.

This intervention is presented by a pair of highly trained woman-identified “near-peer” program facilitators (ie, a few years older than the participants). Unlike the original in-person intervention, a tech facilitator is present at all sessions to facilitate the Zoom technology, troubleshoot participant technical difficulties, assign breakout rooms, provide participants with links to external games/group apps, record sessions, and perform other technical duties before, during, and after each session. The presence of the tech facilitator allows the program facilitators to focus on content delivery and facilitating participant discussion and engagement.

Participants receive the intervention in pairs via Zoom in a private room with enough floor space to practice basic self-defense techniques, and where they know they will not be disturbed. If a pair of participants does not have an appropriate room available to them, a university-sponsored space for each pair is arranged. These Zoom sessions include a minimum of 1 and a maximum of 8 pairs of participants (16 women total) taking part in the intervention together.

#### Control Condition

Participant pairs assigned to the “usual care” control arm will receive one 60-minute session. The workshop focuses on (1) defining consent, including what components need to be present for consent to be meaningful, and (2) expanding the ways in which participants feel comfortable giving, refusing, and asking for consent. The control condition was selected to mimic what is currently available, “usual care” on typical college campuses, which is a brief consent workshop. The content is therefore based on the common components of consent workshops held at the study sites and community-based consent workshops (confirmed with participating campus materials and in consultation with the Ontario Coalition of Rape Crisis Centres).

As with the intervention arm condition, participants receive the consent workshop in pairs via Zoom in a private room (their own or provided to them on campus). These Zoom sessions include up to 8 pairs of participants (16 max) taking part in the workshop together. The control workshop is given by a well-trained RA. Participants who are assigned to the control arm will be informed of the importance of the control group to the study and their ongoing participation. They are made aware that they will be contacted in a year and offered the opportunity to take the full IDEA^3^ program.

### Training of Facilitators and Research Assistants Conducting Interventions

IDEA^3^ has been manualized for program facilitators and tech facilitators and, as is the case for the in-person version of the program, includes scripts, instructions on how to conduct activities, and troubleshooting advice. An EAAA lead trainer delivers the theory and program content-based 5-day facilitator training. Training also includes a certified Wen-Do Women’s Self-Defence instructor leading an in-person 15-hour Wen-Do Women’s Self-Defence Basic Course and another day of instruction in how to safely teach the self-defense content remotely over videoconferencing. Tech facilitators attend a portion of this training and have additional training in their tasks. Program facilitators and tech facilitators receive additional training to perform their research tasks (eg, screening interviews and tracking attendance in REDCap) from PIs. RAs are trained to conduct the control intervention by PIs. Research training of Site/Country Coordinators and RAs is conducted by the Trial Project Manager and PIs.

### Feasibility/Acceptability

#### Postsession Evaluations

At the end of each IDEA^3^ session and at the end of the control arm workshop, participants are given a link to an anonymous 5-minute REDCap survey with closed- and open-ended questions on their evaluation of the session to assess feasibility and acceptability, and allow the chance to offer feedback on the program. Participants are asked to complete the survey immediately to minimize recall bias, and to increase response rates, participants only receive entries into the two $25 raffles for the session if they fill out the evaluation form.

#### Attendance/Dose and Fidelity

Attendance at the assigned intervention/control sessions will be recorded by the tech facilitator/RA to allow us to examine the effects of dose and attrition. All sessions in both arms will be recorded, and a randomly selected 25% of these recordings will be assessed for facilitators’/RAs’ fidelity to the protocols for that arm of the trial. Consent for video recording of each program session is a requirement of participation in the research, is included in the Consent Form, and is discussed in the screening interviews.

### Outcome Assessments

Web-based surveys will be administered to participants at 4 time-points as explained in the following subsections.

#### Baseline Survey

After completing the screening interview and giving consent, participants are invited to complete the baseline survey. The survey includes a number of demographic questions (eg, year of study, age, ethnicity, sex assigned at birth, gender identity, sexual identity, sexual orientation, current relationship status, number of sexual partners, and age of first sexual contact), primary outcome assessment (Sexual Experiences Survey-Short Form Victimization [SES-SFV]) [28], secondary outcomes scheduled for the baseline (Self-defense Self-efficacy Scale) [29], perceived risk for acquaintance SA [30] (1 item), the Perceived Causes of Rape Scale [31], and the Updated Illinois Rape Myth Acceptance Scale [32], and tertiary outcomes (Acceptance of Sexualized Aggression Scale [33], 13 items from the Sexual and Reproductive Empowerment Scale [34]).

#### Postintervention Survey

One week after the completion of the final session for participants in the intervention arm, participants in the same recruitment cohort in both arms of the trial will be invited by email to complete the postintervention survey via the web-based REDCap platform. This survey includes the same measures used in the baseline, excluding demographic questions. It includes additional secondary outcome measures: (1) a measure of Risk Assessment and Resistance developed by Testa et al [35] built on items from Norris et al [36] and Davis et al [37], and (2) an open-ended question measuring knowledge of effective resistance strategies and willingness to use them if a man they knew tried to force them to have sex when they did not want to. It also contains “contamination questions” to determine whether and to what extent participants in the intervention arm shared information with those in the control arm, or control arm participants had IDEA^3^ content shared with them. Participants who indicate on the postintervention SES-SFV that they experienced a completed or attempted rape will also be asked follow-up questions relating to the first (and the most recent if more than one) SA (eg, the date the assault happened, her relationship to the perpetrator, etc) and these same participants will also be asked to complete the Rape Attribution Scale [38] to assess self-blame.

#### 6- and 12-Month Follow-Up Surveys

Participants will be invited to complete the 6- and 12-month follow-up surveys approximately 6 and 12 months after completing their baseline survey. The timing is adjusted to avoid the summer months when response rates are much lower (based on the research team’s previous research). These surveys will consist of the same measures used in the postintervention survey, except that the risk assessment and resistance measure is replaced with 2 different versions of a risk perception task [39], one at each time period, as the risk assessment and resistance measure is not designed for repeat use.

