#### Tertiary Outcomes

The main tertiary aim is to test the hypothesis that IDEA^3^ can positively affect the 6 outcomes shown to be mediators of decreases in SA victimization [47]: (1) increase women’s ability to detect risk in hypothetical situations, (2) increase women’s knowledge of and willingness to use the most effective self-defense strategies, (3) increase women’s confidence that they could defend themselves if confronted with a SA situation, (4) increase women’s perception of their own risk of SA by male acquaintances, (5 and 6) reduce rape myth beliefs and woman-blame that hamper risk detection.

The expanded cognitive appraisal model [48] upon which the intervention is built proposed a process through which changes to the primary outcome of rape victimization would be accomplished. Chained mediation analysis of the original RCT data supported this theory and showed that 3 measures (risk detection, knowledge, and willingness to use effective strategies, and self-defense self-efficacy) were primary mediators that explained 95% of the decrease in completed rape and 76% of the decrease in attempted rape [47]. Other attitudes and beliefs (perceived risk of one’s own SA risk from male acquaintances, general rape myth beliefs, and belief in female precipitation of rape) were more distal mediators that led to improvements in the primary mediators. Measurement of mediators (common to the original EAAA RCT) will allow targeted revision to the IDEA^3^ program if necessary to strengthen program material meant to impact the mediators that were not significantly affected by the intervention.

Tertiary aims additionally include testing the hypothesis that IDEA^3^ can, (7) reduce women’s self-blame if a rape occurs, as previously demonstrated with the in-person version of EAAA, as well as exploratory hypotheses related to whether IDEA^3^ can, (8) reduce attitudes related to acceptance of sexualized violence using the Acceptance of Sexualized Aggression scale [33] and, (9) increase sexual empowerment, using 13 items drawn from the Sexual and Reproductive Empowerment Scale [34].

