### Statistical Analyses

Analyses will be performed after all participants have completed their 1-year follow-up survey. Following a modified intention-to-treat principle, a participant will be included in the analyses if they are randomized and complete one or more postrandomization surveys. The analyses will compare the incidence (ie, first occurrence) of each primary and secondary outcome between the IDEA^3^ and control groups with Kaplan-Meier failure curves (indicating the cumulative percentage of first outcomes among women in the respective groups) and log-rank tests. Participants who are lost to follow-up or drop out will have their data censored at the time of last contact. To account for the correlation between the paired observations, variance estimates will be appropriately inflated for within-pair clustering with the use of estimates of the design effect [50]. In case of baseline imbalances in participant characteristics, Cox proportional hazards regression models with a robust sandwich covariance matrix to account for the clustering will be used to compare the IDEA^3^ and control groups while controlling for the confounding factors. The literature [24,51,52] suggests that prior SA can be a modifier with respect to the effectiveness of SA resistance interventions. Therefore, intervention effects will be compared for women with and without SA histories at baseline by adding a cross-product term to the Cox regression model and testing for statistical significance. For the tertiary outcomes, which are all continuous, linear mixed models will be used to analyze the data that mirror a multilevel repeated-measures study design. A random intercept will be included in the models to account for the correlation between the paired observations, and a first-order autoregressive covariance structure will be used to characterize the interdependence of the repeated measures over time. A cross-product term between group and time will also be included in the models. Participants who are lost to follow-up or drop out can affect the validity of the group comparison if (1) the outcome is related to being lost or dropped, and (2) it is differential between groups. Therefore, baseline characteristics of women who are lost and drop out will be compared with women who complete the trial. In addition, the missing data mechanism will be formally tested [53] to determine whether it is Missing Completely at Random or missing at random. For completeness in assessing the effect of missingness, 2 additional analyses will be conducted: (1) a “per-protocol” analysis among participants who attend all sessions and respond to the 1-year SES-SFV questions; (2) multiple imputation of 5 data sets using a discriminant function for binary outcomes and Markov chain Monte Carlo for continuous outcomes, assuming the missing data mechanism is missing at random.

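### Risk detection and self-blame do not fit the single repeated-measures model set for all tertiary outcomes, and the self-blame comparison is not protected by randomization

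*Protocol article*

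**What the plan says.** The Statistical Analyses section sets one rule: "For the tertiary outcomes, which are all continuous, linear mixed models will be used to analyze the data". The model has a random intercept for the pair. Across visits, "a first-order autoregressive covariance structure will be used to characterize the interdependence of the repeated measures over time", and "A cross-product term between group and time will also be included in the models". No tertiary outcome is exempted.

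**Risk detection** is the first of the six mediators under Tertiary Outcomes. The Baseline Survey section lists no measure of it. The Postintervention Survey section adds one at 1 week: "It includes additional secondary outcome measures: (1) a measure of Risk Assessment and Resistance". (The survey sections call these measures secondary. The Outcome Measures section places the mediators among the tertiary outcomes, and only the tertiary model could apply to a scale score.) The 6- and 12-Month Follow-Up Surveys section keeps the 1-week content "except that the risk assessment and resistance measure is replaced with 2 different versions of a risk perception task", one version per visit, "as the risk assessment and resistance measure is not designed for repeat use".

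**Self-blame** is tertiary hypothesis 7: that the program reduces "self-blame if a rape occurs, as previously demonstrated with the in-person version of EAAA". Under Postintervention Survey, women who report a completed or attempted rape get follow-up questions, and "these same participants will also be asked to complete the Rape Attribution Scale". The 6- and 12-month surveys carry this forward.

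The missing-data text plans MCMC multiple imputation for continuous outcomes under missing at random, and does not exclude self-blame.

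**The concern.** A repeated-measures model with one residual variance and AR(1) correlation assumes the same quantity on the same scale at each visit. Risk detection does not meet that. A change in the arm difference between 1 week and 6 months could come from the switch of instrument and be read as waning or growth. Tertiary Outcomes counts risk detection among the three primary mediators, and Key Findings says the data will show how long effects last.

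Self-blame raises a different problem. It exists only for women with an event that the trial expects to be rarer in the intervention arm. If the program prevents some kinds of assault more than others, the women still assaulted differ between arms in ways that randomization did not balance. A difference in mean self-blame could then appear although the program changed no woman's self-blame, or a real effect could be hidden. For women not assaulted the score is undefined, so a missing-at-random assumption has nothing to act on.

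**Working it through.** **1. The plan's own figures reproduce.** Inputs from Sample Size Considerations: 9.8% vs 6.1%, two-sided 5%, 80% power, design effect 1.031, 10% loss. With p̄ = (0.098 + 0.061)/2 = 0.0795,

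n per arm = [1.960·√(2·0.0795·0.9205) + 0.8416·√(0.098·0.902 + 0.061·0.939)]² / 0.037² = (0.7498 + 0.3212)² / 0.001369 = 837.9, so 838 per arm and 1676 in all.

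1676 × 1.031 / 0.90 = 1919.95, so 1920. The stated power above 99% for risk detection at 1 week also holds: with 838 per arm it exceeds 0.999 at d = 0.54 and at 0.8 × 0.54. No stated figure is disputed.

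**2. Risk detection, visit by visit.**

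| Visit | Measure |
|---|---|
| Baseline | none listed |
| 1 week | Risk Assessment and Resistance measure |
| 6 months | risk perception task, one version |
| 12 months | risk perception task, other version |

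With visit as a category, the model's arm difference at visit t is group + group-by-time(t). It compares randomized groups on one form, so it is valid. The contrast of visit s with visit t is (arm difference on the form at s) − (arm difference on the form at t). From 1 week to 6 or 12 months the two terms are in different units. From 6 to 12 months they share a task, but the article does not say that the versions are equivalent.

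With equal numbers at each visit, a single residual variance is about (s₁² + s₂² + s₃²)/3. Unless the three form-specific SDs are equal, standard errors are too large at visits with a smaller SD and too small at those with a larger one. AR(1) adds that the correlation between adjacent visits is the same within a task as across two different instruments.

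**3. Self-blame: how many women.** Followed per arm: 1920 × 0.90 / 2 = 864. Attempted rape is 9.3% vs 4.6% in Sample Size Considerations. The overlap with completed rape is not given, so both limits are shown.

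- Full overlap: 0.098 × 864 = 84.7 control; 0.061 × 864 = 52.7 intervention; 137.4 in all, 8.0% of the 1728 followed.
- No overlap: (0.098 + 0.093) × 864 = 165.0; (0.061 + 0.046) × 864 = 92.4; 257.5 in all, 14.9%.

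Detectable difference at 80% power, (1.960 + 0.842)·√(1/n_C + 1/n_I), pair clustering ignored:

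- Full overlap: 2.802 × √(1/84.7 + 1/52.7) = 0.49 SD.
- No overlap: 2.802 × √(1/165.0 + 1/92.4) = 0.36 SD.

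Power at d = 0.3 is 40% and 64%.

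**4. Self-blame: how large selection could be.** By hypothesis the program removes q = 1 − 6.1/9.8 = 37.8% of would-be respondents (full overlap) or q = 1 − 10.7/19.1 = 44.0% (no overlap). Illustration, on assumptions not in the documents: half of control assaults are of a type whose self-blame differs by δ = 0.3 to 0.8 SD, and only that type is prevented. Its share among intervention respondents falls to (0.5 − q)/(1 − q) = 0.197 or 0.107. The arm difference with no effect on self-blame is (0.5 − share)·δ:

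- q = 37.8%: 0.09 to 0.24 SD.
- q = 44.0%: 0.12 to 0.31 SD.

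The upper end approaches the smaller detectable difference of 0.36 SD.

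**The case against.** The strongest case against has five parts.

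- **Categorical time.** With visit as a category, instrument means fall into the time main effect and the model still gives the arm difference at each visit. The article does not specify linear time, and its only numerical tertiary target is a 1-week arm difference. This stands. A reader might infer that the group-by-time term compares nothing but scales, or that no change contrast can be read. The text does not support that: within-visit differences are sound, and 6 vs 12 months uses versions of one task. The variance and AR(1) problem and the 1-week-to-later contrast remain.
- **Program revision.** One might infer that apparent waning would misdirect revision. Tertiary Outcomes ties revision to mediators the intervention did not significantly affect, which is an arm difference, so that rule is not driven by a trend.
- **Conditional wording.** The self-blame aim is already limited to women who are assaulted. It would be wrong to say that the protocol claims an unconditional reduction. But the conditioning is what breaks the randomized comparison, and the Abstract still frames it as an effect of the program.
- **Unbalanced data.** A mixed model accepts one or several records per woman. That is so, and a sparse panel alone would not be a fault. The selection and the undefined values are.
- **Condensed article.** Scaling details may sit in a fuller plan. Here, though, the article states a rule for all tertiary outcomes, and the rule does not fit two of them.

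**Conclusion.** The point holds in limited form. For risk detection, the stated covariance model is inappropriate on raw scores and would give wrong standard errors unless the forms happen to share a variance. A trend from 1 week to later visits is uninterpretable, and one from 6 to 12 months depends on unstated equivalence. Arm differences at each visit stand. For self-blame, the comparison is an association among assaulted women, on about 137 to 257 respondents, and can detect only about 0.49 to 0.36 SD. Quoting 85 vs 53 and 0.49 alone would understate the numbers, because attempted rape also triggers the scale.

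This assumes that the two risk measures are the intended measures of risk detection, that the plan's incidences and 10% loss hold, and that every woman reporting an event answers the scale. Women who take the shortened late survey described under Differential Dropout would not, which lowers the counts. The first recall window opens at the baseline survey, so a few events may precede randomization. The bias of 0.09 to 0.31 SD is an illustration, not an estimate. Nothing here shows that an effect on self-blame is absent, and the primary and secondary analyses and the sample size are untouched.

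**What to change.** In Statistical Analyses, exempt the two outcomes from the common model.

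- **Risk detection.** Report standardized arm differences separately at 1 week, 6 months and 12 months with pair-clustered variance. Alternatively, standardize within visit and allow visit-specific variances. Make no time-trend claim across the change of instrument, and compare 6 with 12 months only if the versions are shown to be equivalent.
- **Self-blame.** State that the comparison is conditional on assault and is reported as an association among assaulted women, not as a randomized program effect. Exclude it from the multiple imputation. Optionally add a sensitivity analysis with bounds for women who would be assaulted under either arm.

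The cost is analysis wording only, with no new data and no change in conduct. Data collection runs to May 2027, so it can be settled before analysis. The price is a weaker claim on self-blame and no time trend for risk detection.
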